|  | 
 
- To fill out Myers credibility index checking overall validity of informed consent document
 
- To fill out Acupuncture Belief Scale (ABS) and State-Trait Anxiety Inventory-X (STAI-X)
 
- To measure pressure pain phreshold (PPT) in the non-dominant upper arm
 
 
3. Induction of delayed onset muscle soreness model
 
 
- Measurement of 1 Repetition Maximum (1RM) in the non-dominant arm
 
- Repetitive arm-curl exercise in the non-dominant arm using 1RM weighted dumbbell
 
- Measurement of muscle discomfort in the non-dominant arm with visual analogue scale (VAS)
 
- Measurement of PPT in the non-dominant arm
 
 
4. Acupuncture treatment
 
 
- RA (PC2, LI4, LI11 and LU5 of the non-dominant arm) and PA (two points on the muscle belly of biceps brachii, 1 cun proximally from LI11, and 1 cun laterally from PC2 of the non-dominant arm) will be performed for 15 minutes once daily for three consecutive days with manipulation (by rotating 180 degrees clockwise and counter-clockwise in a frequency of 2 Hz at immediately, 3, 6, 9, and 12 minutes after needle insertion)
 
 
5. After acupuncture treatment
 
 
- To fill out de-qi questionnaire
 
- Measurement of muscle discomfort in the non-dominant arm with VAS
 
- Measurement of PPT in the non-dominant arm
 
 <hr/> 
1. Before acupuncture treatment
 
 
- Adverse event monitoring
 
- Measurement of muscle discomfort in the non-dominant arm with VAS
 
- Measurement of PPT in the non-dominant arm
 
 
2. Acupuncture treatment
 
 
- RA (PC2, LI4, LI11 and LU5 of the non-dominant arm) and PA (two points on the muscle belly of biceps brachii, 1 cun proximally from LI11, and 1 cun laterally from PC2 of the non-dominant arm) will be performed for 15 minutes once daily for three consecutive days with manipulation (by rotating 180 degrees clockwise and counter-clockwise in a frequency of 2 Hz at immediately, 3, 6, 9, and 12 minutes after needle insertion)
 
 
3. After acupuncture treatment
 
 
- To fill out de-qi questionnaire
 
- Measurement of muscle discomfort in the non-dominant arm with VAS
 
- Measurement of PPT in the non-dominant arm
 
 <hr/> 
1. Before acupuncture treatment
 
 
- Adverse event monitoring
 
- Measurement of muscle discomfort in the non-dominant arm with
 
 |

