| 1.4.3 Main outcomes | 
Main outcomes are pain outcomes and blinding of participants
 
 
- Pain outcomes: PPT and VAS.
 
✓ Two way ANOVA is considered as the way of statistical plan as it can analyze the effect of two interventions (acupuncture and informed consent)
 
✓ The effect will be assessed as statistically significant when p value is under 0.05.
 
- Blinding of participants will be analyzed using a Blinding Index (BI, Bang, 2004).
 
                                                                                                                                                                                                                                                                                                                                                                                                                                                                                                                                                                                                                                                                                                                                                                                                                                                                                                                                                                                                                                                                   |

I submit this study protocol to Institutional Review Board of Kyung Hee University.

Date: 2019/07/31

Primary investigator: [name]

[figure not shown]

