| 1                                                                                                                                                                                                                                                                                                                                                                                                                                                                                                                                                                                                                                                                                                                                                                                                                                                                                                                                                                                       | 
1. Retrieval of written Informed consent
 
2. Screening
 
- Measurement of height and weight
 
- To check history of past/present illness, smoking/drinking, and resistance training
 
- To fill out Myers credibility index checking overall validity of informed consent document
 
- To fill out ABS and STAI-X
 
- To measure PPT in the non-dominant upper arm
 |                                                                                                                                                                                                                                                                                                                                                                                                                                                                                                                           |                          |                       |                    |           |                                                                                                                                                                                                                                                                                                                                                                                                                                      |                      |                                       |                      |                                      |          |                                                                     |             |                 |

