|  | 
 
3. Induction of delayed onset muscle soreness model
 
 
- Measurement of 1RM in the non-dominant arm
 
- Repetitive arm-curl exercise in the non-dominant arm using 1RM weighted dumbbell
 
- Measurement of muscle discomfort in the non-dominant arm with VAS
 
- Measurement of PPT in the non-dominant arm
 
 
4. Acupuncture treatment
 
 
- RA (PC2, LI4, LI11 and LU5 of the non-dominant arm) and PA (two points on the muscle belly of biceps brachii, 1 cun proximally from LI11, and 1 cun laterally from PC2 of the non-dominant arm) will be performed for 15 minutes once daily for three consecutive days with manipulation (by rotating 180 degrees clockwise and counter-clockwise in a frequency of 2 Hz at immediately, 3, 6, 9, and 12 minutes after needle insertion)
 
 
5. After acupuncture treatment
 
 
- To fill out de-qi questionnaire
 
- Measurement of muscle discomfort in the non-dominant arm with VAS
 
- Measurement of PPT in the non-dominant arm
 
 
 <hr/> 
 
1. Before acupuncture treatment
 
 
- Adverse event monitoring
 
- Measurement of muscle discomfort in the non-dominant arm with VAS
 
- Measurement of PPT in the non-dominant arm
 
 
2. Acupuncture treatment
 
 
- RA (PC2, LI4, LI11 and LU5 of the non-dominant arm) and PA (two points on the muscle belly of biceps brachii, 1 cun proximally from LI11, and 1 cun laterally from PC2 of the non-dominant arm) will be performed for 15 minutes once daily for three consecutive days with manipulation (by rotating 180 degrees clockwise and counter-clockwise in a frequency of 2 Hz at immediately, 3, 6, 9, and 12 minutes after needle insertion)
 
 
3. After acupuncture treatment
 
 
- To fill out de-qi questionnaire
 
- Measurement of muscle discomfort in the non-dominant arm with VAS
 
- Measurement of PPT in the non-dominant arm
 
 
 <hr/> 
 
1. Before acupuncture treatment
 
 
- Adverse event monitoring
 
- Measurement of muscle discomfort in the non-dominant arm with VAS
 
- Measurement of PPT in the non-dominant arm
 
 
2. Acupuncture treatment
 
 
- RA (PC2, LI4, LI11 and LU5 of the non-dominant arm) and PA (two points on the muscle belly of biceps brachii, 1 cun proximally from LI11, and 1 cun laterally from PC2 of the non-dominant arm) will be performed for 15 minutes once daily
 
 
 |

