| 2.3.9 Statistical plan | 
Main outcomes are pain outcomes and blinding of participants
 
 
- Pain outcomes: PPT and VAS.
 
✓ Two way ANOVA is considered as the way of statistical plan as it can analyze effect of two interventions (acupuncture and informed consent)
 
✓ The effect will be assessed as statistically significant when p value is under 0.05.
 
- Blinding of participants will be analyzed using a Blinding Index (BI, Bang, 2004).
 
- Scores of Myers credibility index, ABS, STAI-X, acupuncture credibility test, and de-qi questionnaire will be analyzed using two-way ANOVA with independent variables (type of acupuncture and placebo information disclosure). A p value less than 0.05 will be considered as statistically significant.
 
- Adverse events will be reported with details and causal relationship with acupuncture will be also assessed. Whether frequency of adverse events that has causal relationship with acupuncture differ between acupuncture types will be analyzed using chi-squared test or Fisher's exact test. A p value less than 0.05 will be considered as statistically significant.
 
- Demographic data will reported descriptively, i.e., continuous variables will be described with mean <math>\pm</math> standard deviation and categorical variables will be shown as frequency (%).
 
                                                                                                                                                                                 |

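### The two-way ANOVA for PPT and VAS names no baseline term although both are measured before the first needling, which costs precision for the acupuncture effect and the interaction

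*Protocol*

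**What the plan says.** Section 1.4.3 of the Protocol names PPT and VAS as the pain outcomes and says of their analysis "Two way ANOVA is considered as the way of statistical plan as it can analyze the effect of two interventions". Section 2.3.9 (Statistical plan) repeats the sentence almost word for word. The two interventions meant are acupuncture type and consent form. Neither section names a covariate, a change score or a repeated-measures term for PPT or VAS. Where 2.3.9 spells out model terms, for the questionnaire scores, it lists the same two factors and nothing else.

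The Day 1 schedule in 1.4.2 and 2.3.4 runs in this order:

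- Consent form.
- Screening, with "To measure PPT in the non-dominant upper arm".
- Arm-curl exercise, followed by "Measurement of muscle discomfort in the non-dominant arm with VAS" and a second PPT.
- First acupuncture session.

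So two PPT values and one VAS value exist for each participant before any needle is applied. Under 2.2.6, one of the two consent forms is handed out at random at the beginning of the study, before all three measurements.

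Section 2.2.4 aims for 80 participants, recruits 89 to allow for 10% dropout, and describes the trial as exploratory, with no effect size or power.

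**The concern.** Part of the spread in a follow-up PPT or VAS is difference between people that was already visible before treatment. A model with only the two design factors leaves that part in the residual. With about 20 participants per cell, chance differences in starting values then widen the confidence intervals.

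The acupuncture-by-disclosure interaction is at stake most. It asks whether the form changes the real-versus-placebo difference, which is one direct reading of the objective in 2.1.2 (the impact of placebo information on study results). In a 2x2 design it is also the least precise estimate. The measurements that would sharpen it are already in the schedule.

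**Working it through.** **Inputs from the Protocol.** Target 80, dropout 10%, 89 recruited (2.2.4); four groups in a 2x2 design (1.4.1, 2.3.3); significance at p below 0.05 (1.4.3, 2.3.9).

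**Assumptions.** Equal allocation (20 per cell, 40 against 40 for a main effect); two-sided test; 80% power; interaction in the model; equal SD at both times; r from 0.3 to 0.8, since the documents give no correlation.

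**The plan's own figure.** 80 / (1 − 0.10) = 88.9, rounded up to 89, as stated. There is no power figure to reproduce.

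**Formulas, in units of the outcome SD.** Residual variance V:

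- ANOVA on the follow-up value: V = 1, with 80 − 4 = 76 error df.
- ANCOVA on the pre-needling value: V = 1 − r², with 75 df.
- ANOVA on change: V = 2(1 − r), with 76 df.

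SE of a main effect = √(4V/80). SE of the interaction (difference of differences) = twice that. The detectable effect is the one giving 80% power under the non-central t distribution.

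**Results.** ANOVA on the follow-up value: main effect 0.63 SD, interaction 1.27 SD. With the covariate:

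| r | 1 − r² | Acupuncture main effect | Interaction | Unadjusted N for the same precision, 80/(1 − r²) |
|---|---|---|---|---|
| 0.3 | 0.91 | 0.61 | 1.21 | 88 |
| 0.5 | 0.75 | 0.55 | 1.10 | 107 |
| 0.7 | 0.51 | 0.45 | 0.91 | 157 |
| 0.8 | 0.36 | 0.38 | 0.76 | 222 |

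For an assumed main effect of 0.5 SD, power is 60% unadjusted and 64%, 72%, 87% and 96% adjusted at these r. A 4,000-run simulation gave 60% unadjusted, and 72% and 87% adjusted at r = 0.5 and 0.7.

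**If the outcome is a change score.** The variance ratio of ANCOVA to change is (1 − r²) / [2(1 − r)] = (1 + r)/2, so the saving is (1 − r)/2: 35%, 25%, 15% and 10% at r = 0.3, 0.5, 0.7 and 0.8. The detectable main effect on change is 0.75, 0.64, 0.49 and 0.40 SD. ANCOVA is still better at every r, but by less as r rises.

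**Which effects may be adjusted.** Needling starts only after these values are taken, so within each consent form they are balanced between real and placebo acupuncture in expectation. Adjustment therefore leaves the acupuncture effect and the interaction unbiased. For disclosure they are measured after randomisation and after the form is read. Suppose the form shifts the pre-needling value by 0.4 SD, the slope is 0.6, and the direct effect on follow-up is 0.30 SD. The total disclosure effect is then 0.30 + 0.6 × 0.4 = 0.54. In a simulation of that case the unadjusted analysis returned 0.54 and the ANCOVA 0.30. The acupuncture effect and the interaction, both set at 0.50, stayed at 0.50 with SEs about 20% smaller (roughly 0.23 to 0.18 and 0.45 to 0.37).

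**The case against.** **The model may not be unadjusted in the end.** The Protocol does not define the dependent variable, and a statistical analysis plan not shown could add a covariate. That is fair, and it is why the change-score comparison is given. But the Protocol is not silent. It chooses a method in two places and gives a reason for it, and that method as named makes no use of the Day 1 values.

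**The correlation may be low.** This stands. The VAS covariate is discomfort right after exercise in a model of delayed soreness, and nothing in the documents shows that it predicts later soreness. At r = 0.3 the gain is small.

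**The trial is about disclosure, and there the covariate comes too late.** This also stands. Sections 2.1.2 and 2.2.6 make disclosure the question, and adjustment could remove part of a real disclosure effect. The gain is secure only for the acupuncture effect and the interaction.

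**Tempting stronger readings.** A reader might infer that chance imbalance biases the comparison. It does not: the ANOVA on randomised groups is unbiased, and its standard error already carries that imbalance. A reader might also take the fall from 0.63 SD to apply to both main effects. The order of consent and measurement in 2.2.6 and 2.3.4 does not support this for disclosure.

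**Conclusion.** The point holds as a matter of efficiency. The named ANOVA leaves Day 1 pre-needling PPT and VAS unused, and using them would make the acupuncture effect and the interaction more precise at almost no cost. The size depends on an unknown correlation and on what the ANOVA is run on. Against an ANOVA on the follow-up value the gain runs from slight at r = 0.3 to equivalent to almost doubling the sample at r = 0.7 (157 against 80). Against change scores it is a variance saving of 35% down to 10% over r = 0.3 to 0.8. Nothing in the planned test is invalid, and the trial is declared exploratory, so the change is advisable and not essential. No gain is claimed for the disclosure main effect.

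**What to change.** In 1.4.3 and 2.3.9, state for each pain outcome:

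- The acupuncture effect and the acupuncture-by-disclosure interaction are estimated from a two-way ANCOVA (acupuncture type, consent form, their interaction) with the participant's Day 1 pre-needling value of the same measure as covariate.
- For PPT, one of the two pre-needling values is prespecified, for example the screening value. For VAS it is the post-exercise value, the only one there is.
- For the disclosure main effect the unadjusted estimate leads and the adjusted one is supportive, because the form is read before the covariate is measured.
- Myers, ABS and STAI-X scores are not used as covariates, because the form itself may change them.

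Cost: a short amendment to the two sections, one error degree of freedom, and two reported estimates for disclosure. No new data, visits or participants are needed.

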| 1.4.1 Methods                                   | 
A 2X2 factorial design randomized clinical trial will be conducted in 4 groups of healthy people.
 

- Two types of acupuncture: real acupuncture and placebo acupuncture

- Two types of informed consent: complete disclosure of false acupuncture information and incomplete disclosure of false acupuncture information

 

Acupuncture	Real acupuncture (RA)	Placebo acupuncture (PA)	

Informed consent			

Full disclosure of placebo information (FD)	RA-FD group	PA-FD group	

Partical disclosure of placebo information (PD)	RA-PD group	PA-PD group	

 
① Intervention 1: acupuncture
 

- Real acupuncture: 0.25X40mm stainless-steel needle (Dongbang, Korea)

- Placebo acupuncture: 0.25X40mm Park Sham Needle (AcuPrime, UK)

 
② Intervention 2: placebo information in informed consent document
 

- Fully disclosed information: to state the information about placebo acupuncture as it is:
"You will be randomly given experimental acupuncture or control acupuncture. Though control acupuncture mimics experimental acupuncture, it does not penetrate the skin because it is fake acupuncture with a blunt needle tip."

- Partially disclosed information: not to state the information about placebo acupuncture as it is:
"You will be randomly given experimental acupuncture or control acupuncture. Control acupuncture is a different kind of acupuncture which has been frequently used in clinical trials as a comparison to experimental acupuncture."

 | Acupuncture              | Real acupuncture (RA) | Placebo acupuncture (PA) | Informed consent                      |              |                                                                                                                                                                                       | Full disclosure of placebo information (FD) | RA-FD group | PA-FD group | Partical disclosure of placebo information (PD) | RA-PD group | PA-PD group |

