| 3.                         | Treatment regimen                                                                                                                                                                                                                                                                                                                                                      | 3a) Number of treatment sessions: three sessions
3b) Frequency and duration of treatment sessions: once daily for three consecutive days                                                                                                                                                                                                                                                                                                                                                                                                                                                                                                                                                                                                                                                                                                                                                               |      |         |                            |                                                                                                                                                                       |                        |                                                                                                                                                                                                                                                                                                                                                                        |                      |                                                                                                                                             |

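### The two-way ANOVA for PPT and VAS ignores that both are measured on five occasions after the first needling, and the protocol names no deciding occasion or effect

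*Protocol*

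**What the plan says.** Section 2.3.9 states "Main outcomes are pain outcomes and blinding of participants", and section 1.4.3 lists "Pain outcomes: PPT and VAS" without ranking them. The model is described as follows: "Two way ANOVA is considered as the way of statistical plan as it can analyze effect of two interventions (acupuncture and informed consent". The decision rule is "The effect will be assessed as statistically significant when p value is under 0.05". For the questionnaire scores, section 2.3.9 spells the factors out: "using two-way ANOVA with independent variables (type of acupuncture and placebo information disclosure". Both factors vary only between participants, in line with the design: "A 2X2 factorial design randomized clinical trial will be conducted in 4 groups of healthy people".

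Treatment is given in three sessions (section 2.3.6: "Frequency and duration of treatment sessions: once daily for three consecutive days"). Sections 1.4.2 and 2.3.4 place "Measurement of muscle discomfort in the non-dominant arm with VAS" and a PPT measurement after needling on Day 1, and both before and after needling on Days 2 and 3. On Day 1 both outcomes are also taken after the exercise and before needling, and PPT is taken once more at screening.

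Neither statistical section names a time factor, a participant term, a baseline covariate, a change or summary score, a deciding occasion or a deciding effect. Section 2.2.4 describes the trial as exploratory.

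**The concern.** The schedule yields repeated values on each person, while the stated model takes one value per person. The analyst must therefore decide what goes into the ANOVA: one occasion, each occasion in turn, or some summary. The protocol does not decide this, yet it attaches a significance verdict to whatever effect comes out. If the choice is made with the data in view, the occasion or outcome that crosses 0.05 can become the headline, and a reader cannot tell which result answers the study question. Section 2.1.4 expects the results to support guidance on consent wording, so that headline would carry weight. The Day 1 pre-needling values, which could sharpen the comparison, are collected and left unused.

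**Working it through.** **Inputs from the protocol**

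- Outcomes: 2 (section 1.4.3).
- Occasions after the first needling: Day 1 after; Day 2 before and after; Day 3 before and after. That is 1 + 2 + 2 = 5 (sections 1.4.2 and 2.3.4).
- Effects in a two-way ANOVA: 2 main effects and 1 interaction, so 3. The protocol does not name the interaction, so this is an upper count.
- Threshold: 0.05 per effect (sections 1.4.3 and 2.3.9).
- Size: 80 participants, 89 with 10% dropout (section 2.2.4). Check: 80 / 0.9 = 88.9, rounded up to 89, which agrees.

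**Assumptions, not in the protocol**

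- Equal allocation, 80 / 4 = 20 per cell.
- Within-person correlation across occasions of 0.3 to 0.9, the same for every pair of occasions.
- PPT-VAS correlation of 0.2 to 0.5.

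**Number of tests if the ANOVA is run at each occasion**

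- All effects: 2 × 5 × 3 = 30.
- Disclosure main effect only: 2 × 5 × 1 = 10.

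**Chance of at least one false positive**

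With k independent tests it is 1 − 0.95^k, which gives 78.5% for k = 30 and 40.1% for k = 10. The tests are correlated, so 10,000 null trials were simulated per setting:

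| Within-person correlation | PPT-VAS correlation | Any of 30 | Any of 10 (disclosure) |
|---|---|---|---|
| 0.3 | 0.2 | 75% | 38% |
| 0.5 | 0.3 | 69% | 32% |
| 0.7 | 0.3 | 61% | 28% |
| 0.9 | 0.5 | 44% | 18% |

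**One occasion or one mean per person**

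This gives 2 × 3 = 6 tests. For the per-person mean, a single test had a simulated type I error of 4.8% to 5.3%. The chance of any false positive over the six is 1 − 0.95^6 = 26.5% if independent, and 24% to 27% in simulation for either the mean or the last occasion.

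**Conditional case: five rows per person treated as independent**

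The variance of an effect is then understated by the factor 1 + (5 − 1) × correlation, and the true type I error is 2 × (1 − Φ(1.96 / √factor)):

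| Correlation | Factor | Formula | Simulated |
|---|---|---|---|
| 0.3 | 2.2 | 18.6% | 19% |
| 0.5 | 3.0 | 25.8% | 26% to 27% |
| 0.7 | 3.8 | 31.5% | 32% to 33% |
| 0.9 | 4.6 | 36.1% | 36% to 37% |

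**The case against.** A reader might infer three stronger claims, and the protocol supports none of them.

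- *That the model can only be run at every occasion or on pooled rows.* A two-way ANOVA on one occasion, one change score or one per-person mean fits the wording equally well and is valid per test. What stands is that the protocol selects none of these.
- *That repeated rows will be pooled.* No section says so. The 19% to 37% error is what would follow if someone did it, not a property of the plan.
- *That the plan promises a 5% error rate overall and fails to deliver it.* The 0.05 is a threshold per effect. Run per occasion, each test keeps its 5%.

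Three further objections have force. The trial is exploratory and claims no power (section 2.2.4), so strict familywise control is not obligatory. Sections 1.3.3 and 2.2.6 say the acupuncture effect is not the true hypothesis, so counting all 30 tests as deciding overstates the exposure; the 10 disclosure tests are the fairer lower count. And a statistical analysis plan that is not shown could settle the occasion, covariates and multiplicity.

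The last objection goes only part of the way. The protocol has its own statistical section, which fixes a model and a verdict threshold that do not fit the repeated measurements in its own schedule. The exploratory status does not remove the free choice of occasion either.

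**Conclusion.** The point holds in a limited form. For pain outcomes measured on five occasions after the first needling, the protocol fixes a between-participant model and a per-effect 0.05 verdict, without time, participant or baseline terms and without a deciding occasion or effect. Analysed occasion by occasion, the chance of at least one false positive is about 44% to 75% over 30 tests, or 18% to 38% over the 10 tests of the disclosure main effect. These ranges rest on assumed correlations, 20 participants per cell and no true effect. They measure the room for selection that the text leaves open; they do not show that the planned analysis is invalid under every reading. The sponsor should correct this, although it does not undermine the design or the data collected.

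**What to change.** For each outcome, replace the two-way ANOVA with one linear mixed model containing acupuncture, disclosure, time and their interactions, with within-person correlation modelled and the Day 1 post-exercise, pre-needling value as covariate. A simpler alternative is an ANCOVA on one pre-named occasion or on the per-person mean.

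Name in advance one occasion or summary and one disclosure contrast, either the disclosure main effect or the disclosure-by-acupuncture interaction, as the main pain result. Report all other occasions and effects as estimates with 95% confidence intervals, and label their p values exploratory. A Holm or Bonferroni adjustment over PPT and VAS (0.05 / 2 = 0.025 each for Bonferroni) is optional in an exploratory trial.

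Costs:

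- Slightly more programming, and fewer results that can be called significant. Visits, measurements and sample size are unchanged.
- If the interaction is chosen, precision is low. With 20 per cell and no baseline adjustment its standard error is √(4 / 20) = 0.45 SD, against √(2 / 40) = 0.22 SD for the disclosure main effect.
- By the schedule, the Day 1 pre-needling values are taken after the consent form has been given. If disclosure already shifts them, the adjusted contrast captures only the further difference. The unadjusted contrast should therefore be reported beside it.
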